## Abstract

**Background:**

Currently there are no disease-modifying treatments for Parkinson’s disease dementia (PDD), a condition linked to aggregation of the protein α-synuclein in subcortical and cortical brain areas. One of the leading genetic risk factors for Parkinson's disease is being a carrier in the gene for β-Glucocerebrosidase (GCase; gene name *GBA1*). Studies in cell culture and animal models have shown that raising the levels of GCase can decrease levels of α-synuclein. Ambroxol is a pharmacological chaperone for GCase and is able to raise the levels of GCase and could therefore be a disease-modifying treatment for PDD. The aims of this trial are to determine if Ambroxol is safe and well-tolerated by individuals with PDD and if Ambroxol affects cognitive, biochemical, and neuroimaging measures.

**Methods:**

This is a phase II, single-centre, double-blind, randomized placebo-controlled trial involving 75 individuals with mild to moderate PDD. Participants will be randomized into Ambroxol high-dose (1050 mg/day), low-dose (525 mg/day), or placebo treatment arms. Assessments will be undertaken at baseline, 6-months, and 12-months follow up times. Primary outcome measures will be the Alzheimer’s disease Assessment Scale-cognitive subscale (ADAS-Cog) and the ADCS Clinician’s Global Impression of Change (CGIC). Secondary measures will include the Parkinson’s disease Cognitive Rating Scale, Clinical Dementia Rating, Trail Making Test, Stroop Test, Unified Parkinson’s disease Rating Scale, Purdue Pegboard, Timed Up and Go, and gait kinematics. Markers of neurodegeneration will include MRI and CSF measures. Pharmacokinetics and pharmacodynamics of Ambroxol will be examined through plasma levels during dose titration phase and evaluation of GCase activity in lymphocytes.

**Discussion:**

If found effective and safe, Ambroxol will be one of the first disease-modifying treatments for PDD.

**Trial registration:**

ClinicalTrials.gov NCT02914366, 26 Sep 2016/retrospectively registered.

## Background

Parkinson’s disease dementia (PDD) is a highly prevalent evolution of Parkinson’s disease [1], believed to result from the aggregation of α-synuclein in subcortical and cortical neurons [2, 3]. Longitudinal studies have shown that by the 10-year follow up from diagnosis, 46% of individuals with Parkinson’s disease had progressed to PDD [4]. Importantly, decline in cognitive function contributes to decreased quality of life [5], increased risk of institutionalization [6] and mortality [7] in individuals with Parkinson’s disease. Therefore, it is not surprising that the development of new therapies to treat cognitive decline has been rated by individuals with Parkinson’s disease and caregivers as one of the top 10 priorities in Parkinson’s disease research [8].

Currently, the treatment for cognition in PDD includes the use of cholinesterase inhibitors in addition to dopaminergic medication [9]. Although somewhat effective in their role of alleviating symptoms, these therapies do not affect the underlying mechanisms leading to progression of the disease and patients get worse despite treatment. Thus, the development of disease-modifying treatments for PDD is critical.

A potential target for disease-modifying treatment is the enzyme β-Glucocerebrosidase (GCase; gene name *GBA1*). GCase is a degradative enzyme that resides in the lysosome and cleaves a neutral glycolipid, glucocerebrosidase, present in the membranes of most cells. Having mutations in both alleles of *GBA1* results in Gaucher disease, which can manifest with hepatic, splenic, hematological and bone abnormalities (Type 1) or with a devastating neurological deterioration that can be rapid or chronic (Type 2 and 3, respectively). However, being a carrier for a pathological mutation in *GBA1* is one of the strongest genetic risk factors for Parkinson’s disease, PDD and Lewy Body dementia. Parkinson’s disease patients bearing *GBA1* mutation, tend to have earlier onset, a greater prevalence of cognitive decline as well as more severe cognitive impairment compared to those without the mutation [10]. In addition, reductions in GCase activity may play a role even in sporadic Parkinson’s disease, as these individuals have low levels of GCase in the brain and cerebrospinal fluid [11–13].

Laboratory studies have demonstrated a direct link between GCase activity and α-synuclein accumulation. In cultured cells, loss of GCase results in α-synuclein accumulation and this process feeds back upon itself, with overexpression of α-synuclein further inhibiting GCase function, and increasing GCase expression reducing α-synuclein [14]. Moreover, reducing GCase genetically [15, 16] or pharmacologically [17] in animal studies results in increased α-synuclein aggregates. Remarkably, overexpressing GCase in the brain of a Parkinson’s disease mouse model reduces α-synuclein and improves cognition [15, 18]. Taken together, these findings suggest that increasing GCase levels could be a therapy that addresses the underlying pathophysiology of PDD to modify the course of disease progression.

Ambroxol is an expectorant that has been available for adults and children over the counter in more than 50 countries for over 30 years [19]. Ambroxol was identified by the [name] Lab in a High Throughput Screen as a pharmacological chaperone of GCase, an agent that stabilizes and increases the levels of GCase [20]. Pharmacological chaperones are small molecules that bind to proteins to stabilize them, increasing the number of protein molecules that fold and function correctly, and thereby reduce the amount of protein degraded. They have been proposed as therapies for a wide range of inborn errors of metabolism, a large fraction of which are caused by mutations which destabilize protein folding, leading to degradation [21–23].

In addition, Ambroxol has good lipophilicity (cLogP = 2.8) and low polar surface area (PSA 58 Å^2^), predicting good CNS penetration. Ambroxol has an excellent safety record and has been studied in > 15,000 patients in more than 100 trials. While the normal expectorant dose in adults is in the range of 75–100 mg/day, doses of 1000 mg IV are used in pregnant women experiencing premature delivery to aid fetal lung maturation, and doses of 30 mg/kg in neonates for fetal respiratory distress syndrome [19].

Although Ambroxol was originally identified as a drug which stabilizes GCase bearing disease-causing mutations which increase its degradation, it is also able to increase the levels of normal GCase [20, 24]. As such, it can markedly increase GCase protein and activity in both normal and Gaucher disease fibroblasts (bearing GCase mutations) at concentrations in the micromolar range [20, 24]. Ambroxol treatment has also been shown to improve lysosomal biochemistry overall by indirect activation of a lysosomal master regulatory gene/transcription factor called TFEB and improved clearance of α-synuclein [25]. More recently, Ambroxol was found to raise GCase levels and lower α-synuclein in induced pluripotent stem cell (iPSC)-derived dopaminergic neurons from *GBA1* mutation patients [26].

In mice, oral Ambroxol for 12 days increased GCase activity in the brainstem, midbrain, cortex, and striatum of wild-type as well as transgenic mice carrying a L444P mutation (i.e. a *GBA1* mutation) [27]. The same study found that transgenic mice overexpressing human α-synuclein treated with Ambroxol had a reduction in α-synuclein levels in the brainstem and striatum compared to untreated mice. Furthermore, Ambroxol reduced S129 phosphorylation of α-synuclein (suggested to play a critical role in α-synuclein aggregation and formation of Lewy bodies and neuritis) in the brainstem by 41% in treated mice compared to untreated mice. Ambroxol has also recently been demonstrated to increase GCase levels in non-human primates [28]. Together, these results support the potential for using Ambroxol as a disease-modifying treatment for synucleinopathies such as PDD.

In pilot studies in humans, Ambroxol was effective at improving GCase function [29, 30]. In a trial aimed at Type 1 (non-neurological) Gaucher disease, 12 patients received 150 mg/day for 6 months, and all but one had some measurable improvement. The best response was in the lightest patient (who received 3 mg/kg/day), suggesting that Ambroxol was under dosed in this study. Ambroxol has also been administered to five Japanese Gaucher disease patients with severe neurological disease, at 25 mg/kg/day or a maximum dose of 1300 mg/day for 6–48 months [29]. Despite their advanced disease, patients had improvements in neurological symptoms (decreased myoclonus and seizure frequency). Improvements in myoclonus allowed two patients to stand steadily, control their balance, and walk again. To our knowledge, no study has tested the effects of Ambroxol on people with Parkinson’s disease or PDD.

The main objectives of the present randomized controlled trial are 1) to demonstrate the safety and tolerability of Ambroxol in patients with PDD, 2) to examine the effects of Ambroxol on cognitive, biochemical, and neuroimaging measures, and 3) to acquire additional pharmacokinetic and pharmacodynamics data for use in future trials. It is hypothesized that Ambroxol will be safe and well tolerated in PDD, and may improve the course of cognitive impairment or motor function, or biomarkers of neurodegeneration in PDD by raising GCase levels in blood and CSF.

## Methods

The study has been approved by Western University Health Science Research Ethics Board (Protocol ID: 105234) and Health Canada (Protocol ID: HC6–24-c181033) in November 2015. The trial has been registered on ClinicalTrials.gov (ID: NCT02914366).

### Design

This is a phase II, single-centre, double-blind, placebo-controlled randomized clinical trial (RCT) using a parallel arm design with a 6-month open label extension period (Fig. 1).

**Fig. 1 Fig1:**
[figure not shown]
Trial flow diagram

### Participants

Participants must fulfill the following inclusion criteria: 1) age greater than 50 years old; 2) Parkinson’s disease (Hoehn & Yahr stage 2–3.5) clearly established for more than 1 year before the onset of dementia; 3) mild to moderate dementia (defined by an upper cut off of a Montreal Cognitive Assessment score of 24 or below and the lower bound by a Mini Mental State Exam of 16 or greater); 4) be on stable doses of medications for motor (i.e. levodopa, dopaminergic agonist), cognitive (i.e. cholinesterase inhibitor), and psychiatric (i.e. antidepressant, antipsychotic) symptoms 3 months prior to the study; and 5) have a responsible caregiver at least 4 days/week. Potential participants will be excluded if they meet one of the following exclusion criteria: 1) have a clinically significant stroke or other neurological condition; 2) have other serious health underlying condition (e.g. cancer or unstable cardiac disease etc.).

Potential participants will be recruited from the Movement Disorders Clinics and Movement Disorders Centre at the London Health Sciences Centre, the Cognitive Neurology and Alzheimer’s disease Research Centre and the Aging Brain and Memory Clinic both at Parkwood Institute (all located in London, ON, Canada), and from community Neurologists that routinely manage Parkinson’s disease. Trial advertisement will be posted on strategic locations, shared in support groups, website, and social media via the Parkinson’s Society South-Western Ontario as well as the online platform Fox Trials Finder. Individuals referred to the study by physicians and those who spontaneously contact the research team will be pre-screened via chart inspection and, if meet inclusion criteria, be offered a Screening visit.

All study visits will take place at Parkwood Institute. MRI scans will be performed at Robarts Research Institute and gait assessment at the Movement Disorders Centre at London Health Sciences Centre all located in London, ON, Canada.

### Screening visit

In the screening visit, the inclusion and exclusion criteria will be reviewed followed by the performance of the Mini-Mental State Exam (MMSE) [31] and the Montreal Cognitive Assessment (MoCA) [32]. Then, participants’ demographic information, medical history, and concomitant medication list will be recorded. A neurological and physical examination will be performed by a Neurologist ([name]). On a separate day, participants will have an MRI scan to rule out possible confounding neurological disease such as stroke or brain tumor and as a baseline for MRI-based biomarkers studies. Individuals with contra-indications to MRI or who choose not to have a MRI scan will have a CT scan. Individuals who pass the Screening visit will complete the Baseline assessment within 28 days.

### Randomization and blinding

Randomization procedure will be completed by pharmacy staff using the website Research Randomizer (https://www.randomizer.org). Eligible participants will be randomly assigned into one of three arms: Ambroxol 1050 mg/day (High-dose), Ambroxol 525 mg/day (Low-dose) or placebo, in a 1:1:1 ratio in blocks of six participants each at baseline. Participants and all research personnel, with the exception of pharmacy staff, will be blinded to the randomization until the study is completed or a patient is purposely unblinded.

For blinding purposes, participants in all three arms will receive the same number of capsules per day. Medication will be blinded by over-encapsulating Ambroxol 75 mg capsules (commercial product) and a matching placebo compound (microcrystalline cellulose) using opaque gelatin capsules (blue colour). Medications are packed as individual patient quantities consisting of one blister card for each week of treatment. The investigational product will be labeled by pharmacy in a double-blind manner (Ambroxol 75 mg/placebo), with pre-assigned participant identification number.

### Intervention

The treatment regimen consists of a titration phase and a maintenance phase. Participants begin the titration phase (weeks 1 and 2) taking 3 capsules a day (225 mg or 150 mg or 0 mg) divided BID (2 capsules in the morning and 1 capsule in the evening). The first medication dose will be taken at the end of Baseline visit and in the presence of the study Neurologist. Possible side effects will be observed for 30 min. Medication dose will increase every two weeks to 6 capsules on weeks 3 and 4, 10 capsules on weeks 5 and 6, and 14 capsules on weeks 7 and 8 divided BID. At the end of titration (week 8) participants will have reached a maximum of 1050 mg or 525 mg or 0 mg per day, depending on group allocation. In the maintenance phase, participants will remain in their maximum dose (1050 mg or 525 mg or 0 mg) from week 9 to week 52 (End of Trial).

### Assessment procedures

Participants will complete 11 visits to Parkwood Institute including baseline, weeks 2, 4, 6, 8, 12, 18, 26, 34, 42, and 52 within one year of treatment. A comprehensive neuropsychological battery will be performed at baseline, week 26, and week 52. The assessment of participants’ motor and neuropsychiatric symptoms will also occur at these time-points. Physical examination will occur at all time-points but weeks 2 and 8, whereas neurological examination will occur at baseline, weeks 6, 12, 18, 34, 42, and 52. Blood and urine samples as well as electrocardiograms will be collected at all visits. Cerebrospinal fluid will be collected through lumbar puncture at baseline, weeks 12, and 52 (optional). Finally, MRI scans will be collected at Screening and week 52 (optional). Table 1 illustrates all assessments performed at each time-point for the duration of the trial.

**Table 1 Tab1:** List of assessments performed in each visit

Visit Name	Screen	Baseline	Week 2	Week 4	Week 6	Week 8	Week 12	Week 18	Week 26	Week 34	Week 42	Week 52
Consent	X											
Medical History												
Medical History	X											
Demographics	X											
Review inclusion and exclusion criteria	X	X										
MRI	X											X
Randomization		X										
Medication												
In clinic first dose		X										
Compliance assessment			X	X	X	X	X	X	X	X	X	X
Concomitant Medication Check	X	X	X	X	X	X	X	X	X	X	X	X
Safety Assessments												
Adverse Event Review		X	X	X	X	X	X	X	X	X	X	X
Interview	X	X	X	X	X	X	X	X	X	X	X	X
Chemistry Blood Draw	X	X	X	X	X	X	X	X	X	X	X	X
Hematology Blood Draw	X	X	X	X	X	X	X	X	X	X	X	X
Coagulation Blood Draw	X	X	X	X	X	X	X	X	X	X	X	X
Genetics Blood Draw		X										
GCase Blood Draw		X	X	X	X	X	X		X			X
Ambroxol Blood Draw		X	X	X	X	X	X		X			X
Urinalysis	X	X	X	X	X	X	X	X	X	X	X	X
Standing Blood Pressure	X	X	X	X	X	X	X	X	X	X	X	X
Seating Blood Pressure	X	X	X	X	X	X	X	X	X	X	X	X
Height	X											
Weight	X	X	X	X	X	X	X	X	X	X	X	X
ECG	X	X	X	X	X	X	X	X	X	X	X	X
Physical Exam	X	X		X	X		X	X	X	X	X	X
Neurological Exam	X	X			X		X	X	X	X	X	X
CSF GCase		X					X					X
CSF Ambroxol		X					X					X
CSF Safety		X					X					X
MMSE	X	X		X	X		X	X	X	X	X	X
Gait Kinematics		X							X			X
Timed up and Go		X							X			X
Purdue Pegboard		X							X			X
UPDRS		X							X			X
Cognitive Assessments												
ADAS-Cog		X							X			X
CGIC		X							X			X
PD-CRS		X							X			X
NPI		X							X			X
CDR		X							X			X
MoCA		X							X			X
Trail Making Test		X							X			X
Stroop test		X							X			X
Geriatric Depression Scale		X							X			X

Legend: *MRI* Magnetic Resonance Imaging, *GCase* Glucocerebrosidase, *ECG* Electrocardiogram, *CSF* Cerebrospinal Fluid, *MMSE* Mini-Mental State Examination, *UPDRS* Unified Parkinson’s disease rating scale, *ADAS-Cog* Alzheimer’s disease Assessment Scale-cognitive subscale, *CGIC* ADCS–Clinician’s Global Impression of Change, *PD-CRS* Parkinson’s disease Cognitive Rating Scale, *NPI* Neuropsychiatric Inventory, *CDR* Clinical Dementia Rating Scale, *MoCA* Montreal Cognitive Assessment

### Primary outcome measures

The primary outcome measures will be the Alzheimer’s disease Assessment Scale-cognitive subscale (ADAS-Cog) [33] and the Alzheimer’s Disease Cooperative Study Clinician’s Global Impression of Change (ADCS-CGIC) [34]. The ADAS-Cog is a comprehensive assessment battery composed by 11 items (word-recall, commands, constructional praxis, naming, ideational praxis, orientation, word recognition, remembering instructions, comprehension, word finding, and spoken language). The test is rated on a scale from 0 to 70, where greater score represents greater impairment. Although designed for Alzheimer’s disease where it is considered a gold standard, the ADAS-Cog has been used effectively in many clinical trials of PDD including large randomized trials [33, 35–38].

The Alzheimer’s Disease Cooperative Study Clinician’s Global Impression of Change (ADCS-CGIC) scale [34] is a 7-point scale for rating patient function in cognition, behavior, and activities of daily living. ADCS-CGIC is a standard test in clinical trials in Alzheimer’s disease and has been useful in trials with PDD [37–39]. This scale was also included because the FDA requires measures of global function in cognitive clinical trials [40]. Thus, this measure will provide critical evidence for potential multi-centre trials in the future. At baseline, information regarding mental/cognitive state (arousal/attention, orientation, memory, language, praxis, and judgment/problem solving), behaviour (thought content, hallucinations/delusions, behaviour/mood, sleep and appetite, and neurological/psychomotor), and functioning (instrumental functional ability and social function) are collected from both patient and caregiver. This information will be used as a reference for the assessment of change throughout the study. In this clinical trial, the individual performing the ADCS-CIGC will be an independent rater blinded to participant’s progression in the trial (i.e. group allocation, compliance, adverse events, and performance in other outcome measures).

### Secondary outcome measures

#### Neuropsychological tests

Secondary cognitive measures include the Clinical Dementia Rating Scale [41], Parkinson’s disease Cognitive Rating Scale [42], Trail Making Test [43], and Stroop test [44].

#### Motor function

The assessment of motor function will be completed using the Movement Disorders Society Unified Parkinson’s Disease Rating Scale (MDS-UPDRS) [45], Purdue Pegboard [46], Timed Up and Go [47], and gait kinematics.

#### Mood and neuropsychiatric symptoms

Neuropsychiatric symptoms will be assessed with the Neuropsychiatric Inventory [48] and Geriatric Depression Scale [49].

#### CSF and brain imaging biomarkers

CSF collected through lumbar puncture (levels of α-synuclein, Tau, phospho-Tau and beta amyloid-42) and brain imaging (brain ventricle and hippocampal volume, and metabolic indicators of neurodegeneration) biomarkers will be collected.

#### Pharmacokinetics and pharmacodynamics

Pharmacokinetics and pharmacodynamics of Ambroxol will be examined through blood concentrations during a dose titration phase and measurements of GCase activity in lymphocytes.

#### Genetics

The *GBA1* gene will be sequenced in all participants to identify carriers and non-carriers of mutations and any other allelic variations in the gene for β-Glucocerebrosidase (GCase; gene name *GBA1*).

### Safety

Routine blood draws (chemistry, hematology, and coagulation) and urine chemistry will be collected in all visits, and any abnormal results will be shared with each participant’s family physician (primary care) with each participant’s permission. Results from laboratory analyses will be reviewed by the study’s principal investigator and periodically by an independent data and safety monitoring board (DSMB).

Each participant will be asked at every visit whether or not any adverse event occurred. Data on adverse events will be reviewed by the study’s principal investigator, recorded in participants’ files, and presented to the DSMB at meetings that occur every 6 months. Serious adverse events (death, hospitalization, or leading to disability/incapacity) will be reported to both Western University research ethics board as well as Health Canada.

Ambroxol is generally well tolerated [50]. The European Core Safety Profile lists headache, dizziness, tachycardia, flushing, nausea, vomiting, diarrhea and abdominal pain as side effects [51]. Recently severe skin lesions such as Stevens-Johnson Syndrome and toxic epidermal necrolysis (TEN) was added as a warning, but it appears to be so rare that it is not possible to determine an event rate. We were unable to identify any literature or case reports of severe reactions. A recent Post Marketing survey of 2707 individuals taking Ambroxol syrup found the 2.5% of patients reported adverse events, which were mostly mild, mainly GI (abdominal pain, diarrhea, nausea, vomiting). There were no serious adverse events.

In the event of minor adverse events (e.g. gastrointestinal side effects), patients will be allowed to spread their dose over a longer interval, or to reduce their dose to the highest dose tolerated. The dose can be advanced again after 2 weeks. For significant but non-threatening laboratory abnormalities, doses can be reduced to the highest dose tolerated. Participants will be allowed to stop taking medication if there is concern about a drug reaction of a clinically significant alteration in laboratory values. They can be re-challenged 2–4 weeks after these abnormalities have resolved.

In order to confirm participant self-reported adherence to the study medication, the number of pills returned in each visit will be counted and recorded. Unused pills will be returned to pharmacy for destruction.

### Sample size

Because Ambroxol has never been used for this indication, there is insufficient information available to perform a sample size calculation. However, it is known that individuals with Alzheimer’s disease typically have 6–7 points change in the ADAS-Cog in 1 year [52] and there are data suggesting that PDD patients may decline in a similar fashion [53–56]. The required sample size was calculated to ensure power of at least 80% in detecting two a priori comparisons, i.e., 1) the difference in average change in the ADAS-Cog scores between patients receiving Ambroxol and placebo, and 2) the difference in the ADAS-Cog scores between low dose Ambroxol and high dose Ambroxol, using 2-sided tests at the 5% significance level. The calculation assumed that the one-year change scores from baseline in ADAS-Cog scores are 7 points, 5 points, and 0 points for placebo, low dose, and high dose groups, respectively, with a common standard deviation of 5.5 points. Using the procedure ‘SAS proc glmpower’ (from SAS version 9.3, SAS Institute Inc., Cary, NC, USA), a total of 60 patients (20 per group) will provide 83.6% power to detect a difference of 2.5 between the average of two Ambroxol groups and placebo, and 80.7% power to a difference of 5 points between the low and high doses of Ambroxol. To account for attrition, 5 additional patients per group will be enrolled in the study.

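### The stated 83.6% power belongs to a 4.5-point pooled Ambroxol-versus-placebo difference, not the printed 2.5 points, for which power is about 37%

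*Protocol article*

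**What the plan says.** In the Sample size section, the protocol article plans for two comparisons of ADAS-Cog change: Ambroxol versus placebo, and low versus high dose. The aim is "to ensure power of at least 80% in detecting two a priori comparisons", and each comparison is to be made "using 2-sided tests at the 5% significance level". The assumed values are "7 points, 5 points, and 0 points for placebo, low dose, and high dose groups, respectively"; the SD is taken to be 5.5 in every arm. From these inputs the section concludes that 60 patients, 20 in each arm, "will provide 83.6% power to detect a difference of 2.5 between the average of two Ambroxol groups and placebo". It gives 80.7% power for the 5-point difference between doses. Five more patients per group are enrolled to cover attrition.

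The Statistical analysis section makes the average of the two Ambroxol arms versus placebo at week 52 the first of the two primary contrasts. The sentence at issue is therefore the trial's statement of its own sensitivity on that contrast.

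**The concern.** The printed difference does not follow from the printed means. The value 2.5 is the average change assumed in the two Ambroxol arms, (5 + 0)/2. It is not the distance of that average from the placebo mean of 7.

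A reader who takes the sentence at face value will believe that a 2.5-point benefit would be missed about 16% of the time (100% − 83.6%). If the true power at 2.5 points is much lower, a non-significant result could be read as good evidence against a benefit of that size when it is not. The Primary outcome measures section looks ahead to possible multi-centre trials. Anyone who sized such a trial from this sentence would make it far too small for a 2.5-point target.

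**Working it through.** **Inputs** (Sample size section unless stated)
- Means: placebo 7, low dose 5, high dose 0
- Common SD: 5.5
- Patients: 20 per group, 60 in total; allocation 1:1:1 (Randomization and blinding section)
- Test: two-sided 5%
- Method: SAS proc glmpower, taken here as a one-way layout with a contrast test, so error df = 60 − 3 = 57 and the critical t is 2.002

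**Step 1. Difference implied by the means**
- Pooled Ambroxol mean = (5 + 0)/2 = 2.5
- Difference from placebo = 7 − 2.5 = 4.5

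**Step 2. Standard errors**
- Placebo versus pooled Ambroxol, contrast (1, −1/2, −1/2): SE = 5.5 × √(1/20 + 0.25/20 + 0.25/20) = 5.5 × √0.075 = 1.506
- Low versus high dose: SE = 5.5 × √(2/20) = 1.739

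**Step 3. Reproduce the protocol's figures** (power from the noncentral t distribution, noncentrality = difference/SE)

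| Contrast | Difference | Noncentrality | Power | Protocol states |
|---|---|---|---|---|
| Low versus high dose | 5.0 | 5.0/1.739 = 2.875 | 80.7% | 80.7% for 5 points |
| Pooled versus placebo | 4.5 | 4.5/1.506 = 2.988 | 83.6% | 83.6%, but for 2.5 points |
| Pooled versus placebo | 2.5 | 2.5/1.506 = 1.660 | 37.2% | not stated |

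The dose contrast reproduces exactly, which supports the method and inputs used here. Working backwards, 83.6% power corresponds to a pooled difference of 4.50.

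**Step 4. Could another reading give 83.6% at 2.5 points?**
- One-sided 5%: 49.8%
- Two-sided 2.5%: 26.8%
- All 25 per group complete: 44.9%
- Normal approximation: 38.2%
- Overall F test on the three planning means: 96.0%

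None does. With 20 per group, the SD would have to be about 3.05 rather than 5.5.

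**Step 5. What the design can detect**
- Smallest pooled difference with 80% power at 20 per group: about 4.3 points
- Expected half-width of the 95% confidence interval: about 2.002 × 1.506 = 3.0 points, which is wider than the printed 2.5
- Patients needed for 80% power at 2.5 points: 58 per group (174 in total); for 83.6%: 64 per group
- If placebo declines by 6 points, the lower end of the 6–7 range quoted for Alzheimer's disease, with the Ambroxol means kept at 5 and 0: difference 3.5, power 62.7%

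**Side calculation.** Under the planning means, the chance that both contrasts are significant is 67.6% (simulation with orthogonal contrasts sharing one variance estimate).

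**The case against.** - **The calculation is sound and only its description is wrong.** This stands. The 83.6% is correct for the assumed means, SD and group size, and neither the sample size nor the primary contrasts are affected. It is a reporting error, not a design error. It still misstates the sensitivity of a primary contrast more than twofold.
- **A reader can recover 4.5 from the sentence before, and the section admits that little was known for planning.** Both are true. But being able to see the contradiction does not remove it, and uncertainty about the inputs does not make the arithmetic right.
- **A null result would be judged by its confidence interval, and a later trial would use this trial's observed data.** Careful readers would do so, and this softens the consequences. It does not justify leaving a false power statement in the protocol.
- **37% rests on an unadjusted comparison of change scores, whereas the planned model adjusts for baseline and uses repeated measures.** This stands as a qualifier. The protocol gives no correlation. If the covariate correlated 0.3 to 0.5 with the change score (an assumption), power at 2.5 points with 20 per arm would be about 40% to 47%. Cutting the SD from 5.5 to 3.05 would take a correlation of about √(1 − (3.05/5.5)²) = 0.83.
- **Joint power is not something the protocol promises.** This stands. Power is stated for each comparison, both exceed 80%, and nothing requires both to succeed. The 68% is useful context and not part of the error.

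**Conclusion.** The concern holds. The Sample size section pairs 83.6% power with a difference of 2.5 points, but its own planning means give 4.5. Under its own model (SD 5.5, 20 per group, two-sided 5%, 57 error df), power is 83.6% at 4.5 points and 37.2% at 2.5. A true 2.5-point difference would therefore be missed about 63% of the time rather than 16%.

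Full completion at 25 per arm raises power at 2.5 points only to 44.9%, and moderate gains from baseline adjustment leave it far below 83.6%. The wrong number is the printed difference. The power figure and the group size agree with the stated assumptions. Correction is required because the statement concerns the first primary contrast.

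**What to change.** In the Sample size section, replace the difference of 2.5 with 4.5 and show its origin (7.0 for placebo versus 2.5 for the pooled Ambroxol arms). Add that, under the same planning model with 20 per group, power for a true 2.5-point difference is about 37%. Leave the 83.6%, the 80.7%, the 20 per group and the enrolment of 75 as they are.

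Optionally, state that the power of at least 80% applies to each contrast separately and that the chance of both being significant is about 68% under the planning means.

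The cost is one corrected sentence and a less favourable account of what the trial can detect. No patients are added and the analysis does not change.
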